# Detection of domestic violence by community mental health teams: a multi-center, cluster randomized controlled trial

**DOI:** 10.1186/s12888-017-1399-7

**Published:** 2017-08-07

**Keywords:** Psychiatry, Domestic violence, Intervention, Victimization, Detection, Patients, Outpatient, Community mental health teams, Randomized clinical trial

## Abstract

**Background:**

Domestic Violence and Abuse (DVA) is associated with a range of psychosocial and mental health problems. Having a psychiatric illness increases likelihood of being a victim of DVA. Despite the evidence of a high risk for DVA and the serious effects of violent victimization in psychiatric patients, detection rates are low and responses are inadequate. The aim of the BRAVE (Better Reduction trough Assessment of Violence and Evaluation) study is to improve detection of and response to DVA in psychiatric patients. In this article, we present the protocol of the BRAVE study which follows the SPIRIT guidelines.

**Methods:**

The BRAVE study is a cluster randomized controlled trial. We will include 24 community mental health teams from Rotterdam and The Hague. Twelve teams will provide care as usual and 12 teams will receive the intervention. The intervention consists of 1) a knowledge and skills training for mental health professionals about DVA, 2) a knowledge and skills training of DVA professionals about mental illness, 3) provision and implementation of a referral pathway between community mental health and DVA services. The follow up period is 12 months. Our primary outcome is the rate of detected cases of recent or any history of DVA in patients per team in 12 months**.** Detection rates are obtained through a systematic search in electronic patient files. Our secondary aims are to obtain information about the gain and sustainability of knowledge on DVA in mental health professionals, and to obtain insight into the feasibility, sustainability and acceptability of the intervention. Data on our secondary aims will be obtained through structured in depth interviews and a questionnaire on knowledge and attitudes on DVA.

**Discussion:**

This study is the first cluster randomized controlled trial to target both male and female psychiatric patients that experience DVA, using an intervention that involves training of professionals. We expect the rate of detected cases of DVA to increase in the intervention teams. With early detection of victimization of DVA in psychiatric patients we hope to improve the mental health of psychiatric patients in the short and long term.

**Trial registration:**

ISRCTN:14115257. Date of registration: 15th January 2015.

## Background

Domestic Violence and Abuse (DVA) is a major public health concern which affects the lives of people across the globe [1]. In the Netherlands approximately 45% of all persons experience at least one form of DVA during their life time and estimates suggest that approximately 200.000 Dutch persons per year are victimized by an intimate partner or family member [2]. DVA is the most prevalent form of violence and affects men, women and children in all segments of society.

The definition of DVA can vary. DVA can be defined as ‘any incident of threatening behaviour, violence or abuse (psychological, physical, sexual, financial or emotional) between adults who are or have been an intimate partner, family member, friend or otherwise closely related (i.e. a care taker or roommate) [3].

In addition to immediate physical injuries and long term conditions such as chronic pain (e.g. back or neck), gynaecologic problems such as chronic pelvic pain or sexually-transmitted diseases and hypertension [4–11], DVA is associated with a range of psychosocial and mental health problems, including loneliness, anxiety, depression, post-traumatic stress disorders, substance abuse and psychosis which can be transient as well as chronic [4, 12–15] [16–18].

Research has found a high prevalence of DVA among psychiatric patients [19] and, across all diagnostic categories, an increased likelihood of being a victim of DVA among women and men with psychiatric disorders [13, 20]. Results from the Dutch nationwide study on victimization in psychiatric patients supports the results and mentioned reports a 6-fold increase of DVA in severely mentally ill (SMI) patients as compared to the general population [20, 21].

Although in the majority of cases of DVA men are perpetrators and women are victims, in the last decade an increasing amount of research showed that, at least among psychiatric patients, men are often victims of DVA as well [22–24]. In other words, despite the absolute DVA prevalence in males is lower compared to females, in psychiatric patients this gender difference is greatly reduced. In patients the risk among men increases steeply compared to the general population, more so than in female psychiatric patients [13, 19, 21, 25]. This phenomenon is mostly overlooked.

In addition because of the social stigma associated with (male) victims of DV and the few studies on male victimization of DVA, under detection in general but in males specifically, is likely as well.

Despite the evidence of a high risk for DVA in psychiatric patients and its serious consequences on patients and their families, detection rates of DVA remain low. Around 10–30% of cases are detected by psychiatric service providers [26]. Clinicians often report barriers to ask for experiences of concurrent DVA. These barriers include the fear to confront and offend patients or the fear to induce false memories [27], and perceived lack of knowledge and expertise to address the abuse [28]. Moreover, after the detection of DVA, treatment plans rarely take these experiences of DVA into account [25]. These figures are alarming and indicate that a great need to invest in interventions to improve the identification of DVA victimization and provision of mental health services addressing the prevention of DVA (re-)victimization among psychiatric patients. Although there is little research on this subject, some have suggested the use of an individual screenings tool to improve detection of and outcomes for domestic violence in women [29]. However, a Cochrane systematic review of screening in primary care found that this did not increase referrals to services specialized in DVA nor did it decrease experienced DVA in victims [29]. These results suggest that information dissemination on DVA to professionals and patients and a screenings tool for DVA in isolation does not create consistent, sustainable improvements in identification and response to DVA.

As was shown in studies [13, 30], identification rate of victims of DVA by health care professionals can increase with a sustainable training of professionals and changes in policy including the implementation of a referral and care pathway within health care systems. Apart from a positive effect on detection rate, these type of interventions result in more referrals to specialist services for DVA [13, 30].

The BRAVE study is informed by the Linking Abuse and Recovery through Advocacy (LARA) pilot study in mental health services and Identification and Referral to Improve Safety (IRIS) cluster trial in primary care conducted in the United Kingdom [13, 30], as both of these studies showed promising results. Detection and referral rates increased after a multi-faceted intervention was provided to clinical teams which included training by the DVA sector and a referral and care pathway which included referral to the DVA sector; the level of functioning and abuse experienced by psychiatric patients in the LARA study was measured and also improved [31]. The BRAVE study is the first randomized controlled trial which focuses on males and females who have a mental illness.

The BRAVE study is an interventional study. The intervention consists of: 1) a knowledge and skills training for mental health professionals about DVA, 2) knowledge and skills training of DVA practitioners about mental illness, 3) the provision and implementation of a direct referral pathway between community mental health services and DVA services for victims of DVA with mental illnesses. The effect of this intervention will be tested in a cluster randomized controlled trial comparing the detection rate of domestic violence in psychiatric patients of community mental health teams in the intervention condition versus teams in the control condition. Furthermore we aim to assess the feasibility, sustainability and acceptance of the intervention for clinicians, policy makers, managers and victims of DVA in both the community mental health services and the DVA services. We expect that the number of detected cases of DVA will increase in the intervention group compared to the control group.

## Methods

### Domestic violence and abuse services in context of the public health system in the Netherlands

In the Netherlands, domestic violence and abuse (DVA) services are part of the public health system. The public health system is financed by government, and services are free of charge for every citizen. The public health services cover a wide range of problems, such as domestic violence, youth work, and housing. Public health services are the responsibility of the municipality. With regards to DVA, starting from 2015, every municipality in the Netherlands has installed a helpline service, for both professionals and victims of DVA, named Veilig Thuis (Safe Home).

A Veilig Thuis-service functions as a gatekeeper. They assess cases of (suspected) DVA, provide advice in cases of (suspected) DVA and coordinate referrals to third party services on DVA. Veilig Thuis (VT) covers both child abuse and intimate partner violence.

All municipal VT-services adhere to national DVA guidelines (diagnostic and referral guidelines). These guidelines are general in nature, which means that slight differences in interpretation and execution may exist between municipalities.

Thus, the municipal care for victims of DVA offers the following services [32].

Informal advice:Assessment: if a person calls the helpline, VT will assess the situation during that phone conversation. The helpline service is available for everyone with a concern regarding DVA. This could be, for example, a co-worker, victim of DVA or a clinician.Advice: after assessment VT will offer advice to whomever using the helpline. This advice ranges from passively monitoring the situation to notifying the police because of a (potentially) dangerous situation. VT can also give referral advice.

Formal advice:Assessment: the helpline can also be used for (health care) professionals who want to ask for a formal advice in a case of (suspected) DVA from VT. This means that VT will be officially involved, they will assess the situation in person and provide an official report after their assessment which includes directives for specialized services.Referral: after assessment, VT will refer the case for the care they deem necessary to stop the violence. This care can vary from empowerment courses delivered by third party DVA services or social work services to temporary eviction of the perpetrator. If a case is deemed dangerous, VT can directly report the case to the police and safeguard the victim through admission in a safe house.

VT employs a variety of professionals namely, doctors specialized in DVA behavioral experts, nurses. Most employees answering the helpline are social workers.

#### Legislation

All professionals working in health care are encouraged to, and in the case of child abuse are obliged to, follow a protocol on (suspicion of) DVA by law. This protocol is called ‘Meldcode’ [33]. Our aim is to improve and further implement this protocol in daily practice as a part of the referral pathway. The Meldcode consists of 5 steps a health care professional should follow when DVA is suspected. The steps are: 1) screening for possible signals of DVA, 2) consultation of a colleague or a DVA professional working at VT, 3) discuss suspicion of DVA with the client/patient, 4) assessment of the severity of the violence. In this step a consultation of a DVA professional at VT is possible, 5) patient referral to a service specializing in DVA (if deemed appropriate) or a formal assessment from VT. If at step 5 the health care professional decides to formally ask advice from VT, VT will assess the situation and refer to/involve the care that they think is needed to stop the violence.

### Study setting

The study will be conducted in the municipalities of Rotterdam and The Hague, the Netherlands. DVA services provided in these municipalities are provided by VT Rotterdam and VT The Hague (see previous paragraph for details). Mental health care in these municipalities is provided by two big community mental health clinics (CMH) i.e. BAVO Europoort (Rotterdam) and Parnassia The Hague. These clinics provide both out-patient and in-patient mental health care and cover the Rotterdam- Rijnmond and the Hague area, which inhabits approximately 2.5 million people. Service use is free of charge for all citizens with health insurance, which is obligatory in the Netherlands, after paying a limited contribution with a maximum of 385 euros per year.

### Ethics

This design takes into account some important dilemmas with regards to studying a population at risk for DVA. In this study, screening for domestic violence is an integral part of the intervention, because it is considered unethical to screen for domestic violence while not offering any kind of help to positively screened patients [34].

There is a high level of acceptance for screening among women with severe mental illness [13, 28]. However, we need to protect professionals and patients from violence as a consequence of disclosure of domestic violence by offering skills and information on how to assess risk of and respond to violence. This theme will be a substantial part of the training of professional and intervention of the patient. Adverse events will be reported to the researcher and scientific committee.

Professionals interested in taking part in the in-depth interviews will be asked to sign an informed consent prior to the interview. Professionals will be recruited by the researcher.

Patients will be asked through their clinicians to participate in an in-depth interview. If patients are interested they will receive an information letter about the study and a researcher will approach the patient to obtain informed consent.

With regards to our primary parameters, data will be collected on team level, and cannot be traced back to individual patients nor clinicians. Data of patients within teams will be stored and analysed anonymously. With regards to our secondary parameters, data on individual professionals (the data of the short questionnaire on DVA and the transcripts of the semi-structured interviews) will be linked to subjects using an identification number. The code list will be stored separately from the anonymous research data, and secured by a password. All data will be stored on local servers in designated folders. Only the research group will have access to these folders. Data will be handled by the research group only.

Due to the nature of this study, there will be no specific post-trial care. We do strive however, to implement champions of DVA in each intervention team and support meetings where participants can ask questions about complicated cases of DVA. While we strive to set up support meetings, these meetings fall beyond the scope of this study.

The Medical Ethical Committee of the Erasmus MC Rotterdam approved the BRAVE study. All amendments will also be approved by the Medical Ethical Committee of the Erasmus MC Rotterdam before publication of any published articles.

### Dissemination

Trial results will be published in scientific journals. Additionally main results will be communicated to the participating mental health institutions. The trial is listed on the ISRCTN registry with study ID ISRCTN14115257.

### Study design

This study is a cluster randomized controlled trial. Clusters in this trial are CMH teams working according to the Flexible Assertive Community Treatment methodology (FACT) [35].CMH teams provide outreaching care to patients with severe mental illness (SMI). A CMH team consists of approximately 10 mental health professionals including a psychiatrist, psychologist, social psychiatric nurses and social workers. Their caseloads consists mostly of patients with schizophrenia, psychosis, bipolar disorder or chronic depression. The level of intensity of care can vary over time and from patient to patient. Each CMH team provides outreaching care for patients living in a certain district of The Hague or the Rotterdam – Rijnmond area. The districts in this study are defined through postal codes. CMH teams included in this study provide care for approximately 200–250 patients.

### Eligibility criteria for CMH teams

Subjects (teams) which meet any of the following criteria will be excluded from participation in this study:Teams providing care to patients <18 yearsTeams with more than 20% of the employees working over different teamsTeams specialized in one specific mental illness (e.g. autism)Teams without a functioning electronic patient file system or with <12 months of historical data at the start of the intervention.

### Sample size

With regards to our primary research aim, we will test the hypothesis that the intervention condition will result in a significantly higher rate of detected cases of DVA compared to the control condition over a 12 month follow up period.

To calculate the sample size needed in this cluster RCT, we started with a sample size calculation assuming individual randomization and inflated this number by a design effect to account for randomization by cluster [36]. This inflation factor (IF) is dependent on average cluster size, and the intra-class correlation (ICC). Using this calculation we found that with a minimum of 12 intervention teams and 12 control teams, with the assumption of a detection rate of 0.25% in control teams (based on the LARA study [13]) and an ICC of 0.03 (based the IRIS study [30]) we will be able to detect a three- to four-fold increase (Beta = 3.55) in the detection rate with a power of 80% and a significance level of 0.05. This calculation assumes an average of 200 patients in every team.

Regarding knowledge and attitudes on DVA, a sample size of 24 teams allows us to detect a large sized increase of knowledge between the intervention and control teams.

In order to answer Aim 2 we will ask a purposeful sample of persons from every profession involved in the study for an in depth interview about the feasibility, sustainability and acceptance of the intervention. A minimum of ten interviewees will be selected from the DVA services, and ten from CMH services. Furthermore all trainers in this study will be interviewed on their experiences. Additionally, we will interview a total of 30 patients or more until saturation of the themes is achieved.

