### Implementation

All members of a CMH team randomized in the intervention condition will be invited to attend the training. Attendance will be monitored. During, and after initial training, teams are actively encouraged to implement the techniques learned in their daily practice.

After the training, clinicians will receive an extended manual incorporating good practice guidelines and information on local/national DVA services. To improve implementation of the knowledge gained in the training, each team in the intervention condition will be recommended to assign a advocate on DVA. Advocates in the intervention teams will collect all problems and questions regarding DVA in their team. We will maintain close contact with the DVA advocates throughout the study through e-mail. Advocates can address problems in the collaboration with DVA practitioners and/or referral to DVA services to the DVA expert team in the institution. This expert team is not part of this study and is already in place at the two participating institutions before the beginning of this study. We will also hand out posters with conversational techniques on DVA and cards team members can use as an aid when talking to their patients about DVA.

The teams in the control condition will not receive any additional training in DVA. Clinicians in the control condition however, can refer patients to DVA services(according to standard practice), when they detect a patient suffering from DVA.2)
*Knowledge and skills training of DVA practitioners about mental illness:*

The professionals working at VT will be offered training on mental illness and procedures within mental health care. The training has been developed by the research team and can be adjusted according to the baseline level of knowledge of the professionals working at VT. Regardless of adjustment, the training consists of a the following key elements:Knowledge on mental illness (including conversational techniques and pitfalls and possibilities in dealing with psychiatric illness)Structure of mental health care services and patient-doctor confidentialityReferral to and communication with clinicians working in mental health care
3)
*The provision and implementation of a direct care pathway between CMH services and DVA services for victims of DVA with mental illness*

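### The 3.55-fold detectable increase does not follow from the stated inputs: with the design effect, a 0.25% control rate gives about 20% power for it, and that single borrowed rate looks low

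*Protocol article*

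**What the plan says.** The Sample size section describes a calculation for individual randomisation, inflated by a design effect that depends on cluster size and ICC. Its inputs are 12 teams per arm, 200 patients per team, 80% power, a significance level of 0.05 (sidedness not given), "an ICC of 0.03 (based the IRIS study [30"]), and a single control rate: "with the assumption of a detection rate of 0.25% in control teams (based on the LARA study [13"]). It concludes: "we will be able to detect a three- to four-fold increase (Beta = 3.55) in the detection rate". The Background section identifies LARA as a UK pilot in mental health services and IRIS as a UK trial in primary care.

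Three Background figures bear on the control rate:
- "approximately 200.000 Dutch persons per year are victimized by an intimate partner or family member"
- "a 6-fold increase of DVA in severely mentally ill (SMI) patients as compared to the general population"
- "Around 10–30% of cases are detected by psychiatric service providers [26"]

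The eligibility section excludes "Teams without a functioning electronic patient file system or with <12 months of historical data at the start of the intervention". The Statistical methods section plans an analysis adjusted for the number of cases detected at baseline.

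**The concern.** There are two problems in the same sentence of the plan. The 3.55-fold figure does not appear to be what the stated inputs deliver. In addition, all of it hangs on one control rate taken from abroad, with no range and no local support.

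The detectable ratio is what a reader will use to interpret a null result. If the trial can really detect only a much larger increase at 0.25%, a null result would not exclude a three- to four-fold effect. If the true usual-care rate is several times higher, the same 24 teams could detect a smaller ratio. The plan's single figure shows neither case.

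**Working it through.** **Inputs (Sample size section).** Control rate p₁ = 0.0025; ratio 3.55, so p₂ = 0.0025 × 3.55 = 0.008875; 12 × 200 = 2,400 patients per arm; ICC 0.03; power 80%; alpha 0.05, taken as two-sided. The 3.55 is read as a rate ratio, as the words three- to four-fold require.

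**Design effect.** 1 + (200 − 1) × 0.03 = 6.97. Effective patients per arm: 2,400 / 6.97 = 344.

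**Power for 3.55-fold.** Power = Φ( (p₂ − p₁) / √{[p₁(1 − p₁) + p₂(1 − p₂)] / n} − 1.96 ).
- Difference: 0.008875 − 0.0025 = 0.006375.
- Variance sum: 0.002494 + 0.008796 = 0.011290.
- With the design effect (n = 344): standard error √(0.011290 / 344.3) = 0.005726; 0.006375 / 0.005726 = 1.113; Φ(1.113 − 1.96) = 0.20.
- Without it (n = 2,400): standard error 0.002169; 0.006375 / 0.002169 = 2.939; Φ(2.939 − 1.96) = 0.84.

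**Ratio detectable with 80% power at 0.25%.**

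| Calculation | Ratio |
|---|---|
| Design effect applied, two-sided | 11.6 |
| Design effect applied, one-sided | 9.7 |
| Design effect applied, 3.55 read as an odds ratio | 11.9 |
| No design effect | 3.4 |
| No design effect, continuity correction | 3.6 |
| No design effect, log-rate scale | 3.6 |

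None of the variants tried reproduces 3.55 with the design effect applied; those without it come close. Even with an ICC of 0.001 the detectable ratio at 200 patients per team is 3.7. For 3.55-fold at ICC 0.03, the number needed is (1.96 + 0.84)² × 0.011290 / 0.006375² ≈ 2,180 per arm before inflation; 2,180 × 6.97 / 200 ≈ 76 teams per arm.

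**How plausible is 0.25%?** This step needs three assumptions that the article does not supply: a Dutch population of 13.5 million (adults) to 17 million (all residents), the 6-fold ratio applied to yearly victims, and the undated 10–30% read as a yearly share.
- 17 million: 200,000 / 17,000,000 = 1.18%; × 6 = 7.1%; × 10–30% = 0.71–2.12%.
- 13.5 million: 200,000 / 13,500,000 = 1.48%; × 6 = 8.9%; × 10–30% = 0.89–2.67%.

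So roughly 0.7% to 2.7%, about 3 to 11 times 0.25%. To reach 0.25% at the lowest detection share, the population would have to be 200,000 × 6 × 0.10 / 0.0025 = 48 million.

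**What 24 teams deliver over a range of control rates** (design effect 6.97 throughout, two-sided 5%; ICC held at 0.03).

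| Control rate | Expected control cases in 2,400 | Power for 3.55-fold | Ratio detectable at 80% |
|---|---|---|---|
| 0.25% | 6 | 20% | 11.6 |
| 0.75% | 18 | 49% | 5.3 |
| 1.5% | 36 | 79% | 3.6 |
| 2.5% | 60 | 95% | 2.8 |

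Exactly 3.55-fold is detectable at a control rate of about 1.53%.

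**The case against.** The strongest reply concerns the control rate. A mental-health-service pilot of the model on which this intervention is based is a defensible source, and a reader might go too far by inferring that the protocol's own figures contradict 0.25%. They do not. The population is not in the article, the three Background figures come from different sources, and nothing there says that they may be multiplied together or that 10–30% refers to 12 months. The Primary outcome section expects cases to be underreported in the records, which pulls the countable rate down. Counting any history of violence, as the Abstract defines the outcome, pulls it up. Multiplying the 45% lifetime figure by 10–30% to get 4.5–13.5% sets a lifetime stock against a 12-month count and should not be used.

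Nor do the local services show that usual care detects more. The Meldcode is obligatory only for child abuse and the trial aims to implement it further. Of the in-house expert team the article says only "This expert team is not part of this study and is already in place at the two participating institutions before the beginning of this study", which tells us nothing about recorded detections.

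It is also true that a higher control rate helps the trial: over 0.75% to 2.5% the detectable ratio runs from 5.3 to 2.8, which brackets 3.55. All of this stands, and it limits the second part of the point. It does not rescue the first. A target that fits a rate near 1.5% is not the target that follows from 0.25%.

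**Conclusion.** The point holds in this form. On the plan's own inputs and method, a 3.55-fold increase from 0.25% has about 20% power instead of 80%, and the detectable increase is about 11.6-fold. A one-sided test does not change the picture (about 30% power, 9.7-fold). The likely explanation is that the design effect was left out of the final figure, but the article does not show the calculation, so this is an inference.

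That 0.25% is too low is plausible and not shown. The 0.7–2.7% range rests on the assumed population of 13.5–17 million and on the two assumptions about the 6-fold and 10–30% figures.

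A reader might infer that the trial is undersized and needs more teams. That does not follow: it holds at 0.25%, but at about 1.5% the 24 teams do detect roughly what the plan claims. The recomputed figures use a normal approximation, which is rough with only 6 expected control cases, and they hold the ICC at 0.03 across control rates, although it was borrowed from primary care.

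**What to change.** Keep 24 teams. In the Sample size section, drop the single 3.55-fold claim and state the sidedness of the test. Give the ratio detectable with 80% power, design effect applied, over a range of control rates: about 11.6 at 0.25%, 5.3 at 0.75%, 3.6 at 1.5% and 2.8 at 2.5%.

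Where feasible, update that table with the usual-care rate and between-team variation found by running the validated search on the 12 months of historical file data. The planned baseline adjustment needs these counts anyway.

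The table costs one reworded paragraph, and the stated detectable effect at 0.25% becomes much less favourable. The update costs more: the keyword piloting and validation and the case-by-case checking of the baseline year would have to be done earlier than planned. No additional teams or patients are needed.

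### The stated sample-size inputs (0.25% control rate, ICC 0.03, 12 + 12 teams of 200) give about 20% power for a 3.55-fold increase, not 80%, and the ICC itself needs justifying at so low a rate

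*Protocol article*

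**What the plan says.** The Sample size section describes a calculation for individual randomization, inflated by a design effect that depends on average cluster size and the ICC. Its inputs are:

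- Control rate: "detection rate of 0.25% in control teams (based on the LARA study [13"), a pilot in mental health services according to the Background.
- Clustering: "an ICC of 0.03 (based the IRIS study [30"). The Background describes that source as the "Identification and Referral to Improve Safety (IRIS) cluster trial in primary care".
- Size: "with a minimum of 12 intervention teams and 12 control teams", and "This calculation assumes an average of 200 patients in every team".

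The result is a "three- to four-fold increase (Beta = 3.55) in the detection rate" with 80% power at a significance level of 0.05. Sidedness is not stated. The section gives no between-team coefficient of variation, and neither the scale nor the outcome rate to which the ICC of 0.03 belongs.

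**The concern.** Two things looked wrong. First, with 200 patients per team an ICC of 0.03 inflates the sample size about sevenfold, yet the printed detectable increase is close to what 2,400 independent patients per arm would give. Second, the ICC of a yes/no outcome is tied to its rate. A value from primary care, carried over to a 0.25% outcome, may imply far more variation between teams than was intended.

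At stake is how the result is read. If the trial has 20% power and not 80% for the increase it names, a null result says little about whether the training works. A reader relying on the stated 80% would take it as fairly strong evidence against an effect of that size.

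**Working it through.** **Inputs (Sample size section).** p1 = 0.0025; ratio 3.55, so p2 = 0.008875; m = 200; 12 teams, hence 2,400 patients, per arm; ICC = 0.03; alpha 0.05 (two-sided unless noted); power 80%.

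**1. Attempt to reproduce 3.55**

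- Design effect = 1 + (200 − 1) × 0.03 = 6.97.
- Effective size per arm = 2,400 / 6.97 = 344.3.
- Power = Φ{[(p2 − p1)√n − 1.96√(2p̄(1 − p̄))] / √[p1(1 − p1) + p2(1 − p2)]}, with p̄ = 0.0056875.
- With n = 344.3: (0.006375 × 18.56 − 1.96 × 0.10635) / 0.10625 = −0.85, so power = 19.8%.
- Solving for the ratio at 80% power gives 11.6, an intervention rate of 11.6 × 0.25% = 2.9%.
- A 3.55-fold increase needs 2,184 independent patients per arm. Inflated, that is 2,184 × 6.97 = 15,222, or about 76 teams of 200 per arm.

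The printed figure is not reproduced, and no variant tried rescues it:

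- One-sided: 9.7-fold, with 29.7% power at 3.55-fold.
- Unpooled, log-rate or arcsine methods, one- or two-sided: 8.3- to 21.9-fold.
- 3.55 read as an odds ratio: 19.6% power.
- 250 patients per team: 11.4-fold.
- A tenfold slip in the control rate (2.5%): 2.82-fold.

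**2. What 3.55 does correspond to**

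- ICC = 0: detectable ratio 3.39, power at 3.55-fold 84%.
- Largest design effect compatible with 3.55: 2,400 / 2,184 = 1.099, so ICC = 0.099 / 199 = 0.0005. This is 60 times smaller than the stated 0.03.

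**3. What ICC 0.03 means at 0.25%**

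On the proportion scale ICC = k²p/(1 − p), where k is the between-team coefficient of variation, so k = √[ICC(1 − p)/p].

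- Control: √(0.03 × 0.9975 / 0.0025) = 3.46.
- Intervention: √(0.03 × 0.991125 / 0.008875) = 1.83.

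As an illustration, if true team rates followed a beta distribution (an assumption), about 85% of control teams of 200 would record no case. With no between-team variation the figure is 0.9975^200 = 61%.

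**4. Sensitivity to clustering**

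The values of k below are assumptions; the article gives none. Model A holds k constant in both arms: variance per arm = [p(1 − p)/200 + k²p²]/12, non-central t on 22 df. Model B holds the ICC constant in both arms: design effect as in step 1, normal approximation.

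| k | ICC at 0.25% | A: power at 3.55-fold | A: detectable ratio | B: power at 3.55-fold | B: detectable ratio |
|---|---|---|---|---|---|
| 0.25 | 0.00016 | 77% | 3.7 | 82% | 3.44 |
| 0.5 | 0.0006 | 67% | 4.3 | 79% | 3.59 |
| 1.0 | 0.0025 | 43% | about 12 | 67% | 4.17 |
| 3.46 | 0.03 | – | not reached | 20% | 11.6 |

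Under Model A with k = 3.46 the standardized difference can never exceed √12 / 3.46 = 1.0, so 80% power is out of reach. The two models must not be mixed in one table column: at k = 1.0 they give about 12 and 4.17.

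**The case against.** The strongest defence is that 3.55 may be about right even if the text around it is wrong. Under Model B, k from 0.25 to 0.5 gives 3.44 to 3.59. If 0.03 is too high for this outcome, a calculation truly built on it would have been conservative. This stands in part: the article does not show that the trial really has 20% power, only that its stated inputs give 20%. It does not rescue the paragraph, which names 0.03 as the value used. Under Model A, power at 3.55-fold stays below 80% at every k from 0.25 to 1.0.

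A reader might also infer that 0.03 is simply impossible or not credible here. The documents do not support that. A coefficient of variation of 3.46 is mathematically possible (the maximum at this rate is √(0.9975/0.0025), about 20). Teams cover districts of differing socio-economic status, and detection depends on what clinicians record. If 0.03 were a latent logit-scale ICC (an assumption), the between-team SD of the log-odds would be √(0.03 × 3.29 / 0.97) = 0.32, and k about 0.33, which is unremarkable. The fault would then lie in putting that value into the inflation factor. Without scale or base rate, the article cannot settle this.

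Nor can one infer that the printed 3.55 was distorted by the borrowed ICC: it was evidently not built on it. Borrowing an ICC from a related trial is an ordinary planning judgement.

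**Conclusion.** The point holds in two parts of unequal strength.

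- **Demonstrable:** the stated rate, ICC, team number and team size give a detectable increase of about 11.6-fold and about 20% power at 3.55-fold, not 3.55-fold at 80%. This rests on the standard design effect that the section describes and on a two-sided 5% test. One-sided testing gives 9.7-fold and about 30%, which does not change the conclusion.
- **Questionable, not shown to be wrong:** an ICC of 0.03 read on the proportion scale implies a between-team coefficient of variation of 3.46 at 0.25%. A correction that keeps 0.03 would rest on an unsupported input. One that silently drops it would hide the mismatch.

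Until both are resolved, the increase that 24 teams can detect is unknown within a wide range. The design is not invalidated.

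**What to change.** Rewrite the power paragraph with the team numbers unchanged, in one of two ways:

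1. Keep ICC 0.03 and report what it delivers: about 11.6-fold detectable at 80% power, or about 20% power at 3.55-fold.
2. Replace it with a value justified at the trial's own detection rate, stating its scale and the base rate it comes from, and recompute. Say openly that the printed 3.55 did not follow from 0.03.

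In either case state the sidedness and add a sensitivity range under a single model. With constant k and t on 22 df, for example, power at 3.55-fold is about 77%, 67% and 43% at k = 0.25, 0.5 and 1.0.

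Historical files can inform k, because the eligibility criteria exclude "Teams without a functioning electronic patient file system or with <12 months of historical data at the start of the intervention". They cannot fix it precisely: at 0.25% a team of 200 yields 0.5 expected cases a year, about 12 over all 24 teams. The range should therefore stay in the text.

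The cost is one recalculation and a reworded paragraph. The downside is that the stated detectable increase becomes less favourable.
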